### Tracking implementation progress at intervention DFs

Conclusions drawn from the data gathered in this trial will highly depend on the module choices at the individual DFs, as well as on the amount of time intervention DFs spend on implementing program activities. To assess intervention dose and fidelity, intervention DFs will therefore be provided with paper-and-pencil calendars to track implementation progress at individual DFs over a period of 12 months. Using these calendars, DF staff will document module choices, as well as module-specific environmental changes and activities at intervention DFs every week. To foster compliance, the calendar is kept simple and easy to use. Directly after the baseline assessment, intervention DF groups receive the calendars including calendar pages for 12 months. Every three months, DF staff will be prompted to send the completed calendar pages back to the research team via mail. The calendar covers program-associated activities from the modules “*diet*”, “*physical activity*”, “*mental well-being*” and “*parental participation*”. For each module, intervention components are listed (e.g., “drinking oasis”, “colorful garden” healthy breakfast buffet, card boxes). The DF staff will be asked to mark the checkboxes, as well as to document the weekly amount of time (in minutes) spent on working with certain intervention materials (e.g., card boxes, wooden train).

#### Qualitative research to gather information about facilitating and hindering factors regarding program implementation at intervention DFs

Four focus group discussions with DF staff, parents, and children will be held at intervention DFs throughout Germany to gather information about factors facilitating or hindering program implementation and general program acceptance. Participating DFs will be randomly selected per geographic region. Attendance of five to ten persons will be intended per focus group discussion at each DF. Focus group discussions will be led by a researcher of the project team, using an adapted focus group guide from a previous study [31]. Researchers leading the focus groups will obtain an informed consent from participants.

### Analysis strategy

#### Quantitative analysis

To evaluate intervention effectiveness, changes in body composition, health behaviors, and psychological outcomes from pre- to post-test among children at intervention DFs will be compared to those observed in children enrolled at delayed intervention control DFs. In addition to descriptive data analyses, quantitative analyses will be performed involving simple two-sample t-tests, as well as mixed effects regression models. Such regression models account for the clustered structure of the data, allow for controlling of baseline differences between the groups and for considering potential confounders, such as age, gender, or parents’ educational attainment, simultaneously. All statistical analyses will be carried out using SAS 9.3 software (SAS Institute Inc., Cary, NC) [32].

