### Study design

Due to the risk of cross-contamination of intervention effects, it was not feasible to allocate children to the intervention or non-intervention conditions at individual DFs [21]. Randomization of DFs to intervention vs. control conditions was also not possible (see below for reasons and recruitment of DFs in the study). Therefore, this study was planned as a CCT with a non-random allocation procedure. CCT designs are used not only to evaluate group interventions but also individual interventions where group level effects are relevant [22]. Therefore, clusters in this study constitute the kindergarten groups of the individual DFs (one group per DF). These clusters will be allocated to intervention and control groups and outcomes will be measured among individuals within those clusters.

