### Sample size

Sample size was calculated with regard to the two primary outcomes diet and PA. Based on a prevalence of fruit consumption reported in a previous study conducted at 64 German DFs including 2.658 preschoolers which reported rates of fruit consumption of 66.7% in the intervention group and 56% in the control group [23], we assumed a difference in the change in diet from baseline to 12-months follow-up of 8% between intervention and control group considering an estimated intracluster correlation coefficient (ICC) of 0.02, 90% power, and α = 0.05 (two-sided). Based on this, we estimated that a total of 1.020 children at 68 DFs would be required for our study. With regard to more conservative estimates for the ICC, this sample size will provide more than 80% power to detect changes of 8% in fruit consumption. We assumed a 25% loss to follow-up twelve months post-baseline. Therefore, we aim to reach 1360 children, in total, at baseline, twenty children at each of the 68 participating DFs. According to De Bock et al. [24], little is known about the extent to which PA-related outcomes in preschool children are inter-correlated. Therefore, our sample size calculation for detecting changes in objectively measured PA is based on the conservative assumption of an ICC of 0.1. To detect a difference of 0.5 standard deviations between intervention and control groups, we assumed a standard deviation of 38 counts per 15 s [24], a power of 90%, and α = 0.05 (two-sided), and estimated that a total of 360 children at 24 DFs will be necessary for our study. We increased our recruitment goal to 20 children per DF (240 per arm) to account for a 25% loss to follow-up. All power calculations were carried out in PASS [25], using tests for two proportions in a cluster-randomized design function.

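### The two-sample t-tests listed for effectiveness ignore clustering: run on children at the planning ICCs, their type I error is about 8.3% (diet) or 20.6% (accelerometry), not 5%

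*Protocol article*

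**What the plan says.** The Quantitative analysis section sets out the comparison: "To evaluate intervention effectiveness, changes in body composition, health behaviors, and psychological outcomes from pre- to post-test among children at intervention DFs" are to be compared with those at delayed intervention control DFs. It then says, in addition to descriptive analyses, that "quantitative analyses will be performed involving simple two-sample t-tests, as well as mixed effects regression models". The next sentence describes the second method only: "Such regression models account for the clustered structure of the data, allow for controlling of baseline differences between the groups". It adds that these models can take confounders into account. Nothing comparable is said of the t-tests, and their unit of analysis is not named.

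The Study design section says that "this study was planned as a CCT with a non-random allocation procedure". The cluster is one kindergarten group per DF, and "These clusters will be allocated to intervention and control groups and outcomes will be measured among individuals within those clusters".

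The Sample size section uses an ICC of 0.02 for diet. For accelerometry the calculation "is based on the conservative assumption of an ICC of 0.1". Both use a two-sided alpha of 0.05.

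**The concern.** A two-sample t-test on children treats the children of one DF as independent observations. The sample size calculation says that they are not. The standard error is then too small, the confidence interval too narrow and the p-value too low, for a reason built into the design and known in advance.

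The t-tests are named as a method for judging effectiveness, apart from the descriptive analyses. The article's own contrast shows that only the regression models deal with clustering and baseline differences. A significant child-level t-test could therefore be presented as evidence that the program works when the real chance of that result under no effect is well above 5%.

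A second, separate weakness is that the health insurer determines when DFs start the program, so the arms may differ in ways that affect the change over one year. A simple t-test has no means of adjusting for this.

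**Working it through.** **Inputs** (Sample size section unless noted)

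- Completers per DF: 1020 / 68 = 15 for diet; 360 / 24 = 15 for accelerometry.
- ICC: 0.02 for diet; 0.1 for accelerometry.
- Alpha: 0.05 two-sided, so z = 1.96.
- DFs per arm: 34 in the full trial; 12 in the accelerometer subsample (Assessments section).

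**The plan's own figures.** The article states no type I error for the t-tests other than the nominal 5%. Its loss-to-follow-up step reproduces: 1020 / 0.75 = 1360 = 68 × 20, and 360 / 0.75 = 480 = 24 × 20, or 240 per arm. This confirms 20 children per DF at baseline and 15 at follow-up. The accelerometer total itself does not reproduce at 15 per DF: 85 per arm for 0.5 SD at 90% power, times 2.4, times 2 arms, gives 408 and not 360. The pair of proportions behind the 1020 is not stated. These are separate questions. The check below needs only cluster size, ICC and alpha.

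**Step 1: design effect.** DE = 1 + (m − 1) × ICC, with m = 15.

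- Diet: 1 + 14 × 0.02 = 1.28.
- Accelerometry: 1 + 14 × 0.1 = 2.40.

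**Step 2: standard error.** The child-level t-test understates it by √DE: √1.28 = 1.13 and √2.40 = 1.55.

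**Step 3: true type I error.** This is 2 × [1 − Φ(1.96 / √DE)].

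| ICC | m | DE | True type I error |
|---|---|---|---|
| 0.02 (diet) | 15 | 1.28 | 8.3% |
| 0.1 (accelerometry) | 15 | 2.40 | 20.6% |
| 0.05 (assumed, not in the article) | 15 | 1.70 | 13.3% |
| 0.02, no loss to follow-up | 20 | 1.38 | 9.5% |
| 0.1, no loss to follow-up | 20 | 2.90 | 25.0% |

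The first two rows are the finding. The others show sensitivity only; a change score needs follow-up data, so 15 per DF is the relevant size under the planned 25% loss.

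**Step 4: check by simulation.** With 8000 null trials per setting, normal outcomes and 15 children per DF, the child-level t-test rejected in 8.3% (ICC 0.02, 34 DFs per arm) and 21.5% (ICC 0.1, 12 DFs per arm). A t-test on DF means from the same data rejected in 4.9% and 5.5%. The excess therefore comes from the unit of analysis and not from the t-test as such.

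**The case against.** The strongest reply is that a valid analysis is already in the plan. Mixed models are listed, the reason for them is given, and the sample size allows for clustering, so the authors have not overlooked it. This stands and it limits the point. A reader might infer that the trial's conclusions carry a false-positive risk of 8% to 21%. The article does not support that: the figures belong to the child-level t-tests, and the mixed models are not affected. Nor is it a defect in itself that the two methods are not ranked, since a condensed article may leave that to the analysis plan. What remains is that an unsuitable test is positively named for effectiveness.

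Other limits also stand:

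- The child as unit of the t-test is an inference. It is the natural reading, because the section compares changes among children and credits only the regression models with handling clusters, but it is not stated.
- No ICC is given for body composition, motor skills or well-being, so no error rate can be derived for them. The ICC of 0.1 is described as conservative and is not given for a change score.
- A reader might attribute part of the inflation to non-random allocation. The calculation contains only the clustering term. Confounding bias would be additional, and nothing in the article allows it to be quantified. It is also partly addressed: DF heads supply socio-economic and migration data for later matching, and comparing changes removes differences in baseline level.
- A reader might add that a t-test cannot suit fruit consumption because it was powered as a proportion. The analysis section does not say that diet will be analysed as yes/no; the questionnaire is a quantitative food frequency instrument, and the Expected results section speaks of increases in consumption.

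**Conclusion.** The point holds in this limited form. The article names simple two-sample t-tests for evaluating effectiveness in a trial that allocates clusters. Run on children, they have a true two-sided type I error of about 8.3% at the diet ICC and about 20.6% at the accelerometer ICC, against a nominal 5%. Equivalently, nominal 95% intervals would cover about 91.7% and 79.4%.

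The figures rest on four assumptions: the t-tests use children as units; the planning ICCs apply to the changes; 15 children per DF complete follow-up; and matching of DFs does not reduce the between-DF variation. A smaller ICC of change would bring the error closer to 5%. The inability of the t-tests to adjust for confounders is a separate, unquantified weakness.

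**What to change.** In the Quantitative analysis section, take child-level two-sample t-tests out of the effectiveness analysis. If t-tests are kept, either run them on DF means (34 versus 34; 12 versus 12 for accelerometry) or label them as descriptive. Add one sentence stating that conclusions on effectiveness rest on the planned mixed model, with a random DF effect and adjustment for the child's baseline value.

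The cost is a change of wording, and wider intervals from any t-tests that are kept. No new data, recruitment or measurement is needed. Further model detail can be left to the analysis plan.

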#### Qualitative analysis

Qualitative focus group discussions will be protocolled by one researcher and audio-recorded. The audio-records will be transcribed, using the software f4. Deductive methods will be used for analyzing the data. Based on the interview guide, an analysis matrix with different categories will be developed. The content of the final protocols will be transferred to each category of the analysis matrix.

### External advisory board

An advisory board of national researchers with expertise in the promotion of healthy dietary patterns, PA, and mental well-being in children will provide advice regarding the development of the assessment battery and the focus group guide. After that, the research team will provide regular status updates on the project to the advisory board (at least three times during the funding period).

### Expected results

We expect that children participating in the program demonstrate greater improvements in body composition, motor skills, dietary and PA patterns, and mental well-being over the course of 12 months than those not participating in the program. For example, we expect greater increases in the scores of the KiMo test, fruits and vegetable consumption, time spent on moderate to vigorous PA, and health-related quality of life, and more pronounced reductions in sitting time and un-sweetened beverage consumption among children participating compared to those not participating in the program.

## Discussion

The provision of evidence-based multi-component interventions to young children under “real-world” conditions which promote healthy eating, PA, and mental well-being is currently very limited in Germany. Thus far, only few multi-component interventions have been implemented and scientifically evaluated at German DFs. Also, implementation research investigating implementation processes, as well as individual or environmental factors facilitating implementation of such interventions, is still lacking [33]. Results of this study will provide new information regarding the effectiveness of a health insurance developed multi-component intervention which targets children’s individual health behavior and changes in the daycare environment. We hope to obtain new insights into the implementation and effects of this program for researchers and stakeholders in the preschool setting and to derive recommendations for the uptake and implementation of such programs in the future.

## Abbreviations

CCT: Cluster-controlled trial
DEGS: German Health Interview and Examination Survey for Adults
DF: Daycare facility
GSE: General self-efficacy
HAPA: Health Action Process Approach
HLS-EU: European Health Literacy
ICC: Intracluster correlation coefficient
IDEFICS: Identification and Prevention of Dietary and Lifestyle-induced Health Effects in Children and Infants
KIGGS: German Health Interview and Examination Survey for Children and Adolescents
PA: Physical activity
PSS: Perceived Stress Scale
SDQ: Strengths and Difficulties Questionnaire
SF: Short Form
WHO: World Health Organization
